# “Bayis Ilh Tus – a strong breath” a community-based research project to estimate the prevalence of chronic obstructive pulmonary disease in remote and rural first nations communities in Canada: research protocol

**DOI:** 10.1186/s12939-020-01240-1

**Published:** 2020-07-24

**Keywords:** Chronic obstructive pulmonary disease, Prevalence, First nations

## Abstract

**Background:**

Respiratory health conditions appear to be more common among First Nations people versus non-First Nations people in Canada. However, the prevalence of chronic obstructive pulmonary disease (COPD) and its associated risk factors in First Nations communities are unknown. This project aims to estimate the prevalence of COPD in several First Nations communities in British Columbia, Canada and to characterize respiratory symptoms, COPD risk factors, and healthcare utilization.

**Methods:**

This project is approved by both the University of British Columbia and Carrier Sekani Family Services Research Ethics Boards. We will randomly sample 220 adults, 30 years and older, from 11 participating First Nations. Each participant will complete pre- and post-bronchodilator spirometry tests and the adapted American Thoracic Society Epidemiological Questionnaire with items about smoking history, respiratory symptoms, co-morbidities, and exposures, in order to identify the presence of COPD and its associated individual, occupational, and community risk factors. Homes will be assessed for air quality measures including particulate matter, carbon monoxide and carbon dioxide, and humidity. Health care utilization will be abstracted from the electronic medical record.

**Discussion:**

This is the first project in Canada to estimate the prevalence of COPD in First Nations communities using a random-sampling approach to recruitment. Additionally, although this study will collect detailed information on smoking history, we will also characterize past and current risk factors beyond cigarette smoking. Finally, our methodology ensures that the benefits to the communities are realized during the study period. Individual results will be shared with individuals and health providers to facilitate care. Air quality results will be sent to each Nation’s governing council to facilitate remediation where necessary.

**Trial registration:**

The study has been retrospectively registered at clinicaltrials.gov (NCT04105088).

## Background

For the First Nations people in Canada, many determinants of disease, including chronic lung disease, are fundamentally related to the ongoing impacts of colonialism and, more specifically, government practices including forced attendance at residential schools and removal of children from their families for placement in to non-Indigenous adoptive homes [1]. With respect to chronic obstructive pulmonary disease (COPD), although the First Nations people have a wealth of knowledge related to health and wellness [2], the impacts of colonization and subsequent past and current harmful government policies introduced several individual- and population-level factors which negatively influence lung health and increase the risk for COPD.

Cigarette smoking (also termed non-traditional tobacco smoking in First Nations settings) is the most common individual lifestyle factor known to cause COPD [3] and was introduced to many communities post-colonization. Across Canada, more First Nations people smoke cigarettes compared to the general population (39% versus 20.5%) [4]. Moreover, the rate of cigarette smoking among First Nations has not substantially declined from 1997 to 2018 [5], while the smoking prevalence among all Canadians has decreased significantly across the same time period [4]. In the Canadian province of British Columbia, the current prevalence of cigarette smoking in Indigenous populations is approximately twice that of non-Indigenous populations (39–40% versus 18–23%, respectively) [4] with a similar trend seen for marijuana smoking [6], further increasing their risk.

Several population-level factors also negatively impact First Nations people’s lung health. Children who attended residential schools were exposed to poor air quality in unheated, poorly-ventilated buildings, had minimal access to appropriate nutrition or health care, and subsequently had high rates of childhood respiratory tract infections [2], a known risk factor for COPD [3]. As the last residential school closed in 1996, many of those children are adults today. The creation of the reserve system (where First Nations people lost their traditional territory and were forced to live in small communities) also changed seasonal patterns of hunting and harvesting and caused a reliance on western-based sources of food. This resulted in a more sedentary lifestyle, another risk factor for poor health [7].

Disparities in access to primary health care services may also influence the development of COPD in First Nations people. Limited access may be due to lack of services, especially in remote and rural communities, but are also due to decades of systemic discrimination against First Nations people [8]. Lack of appropriate primary health care can result in high emergency and acute care utilization, and indeed, the hospitalization rate for respiratory infections and asthma is at least three times higher for rural and urban First Nations than non-First Nations populations in Canada based on the 2006 Canadian Census [9], even after correcting for income level. Similarly, respiratory-related emergency use for asthma and COPD for First Nations is more than double compared to the non-First Nations population [10]. Housing problems also remain a factor, as many houses on First Nations reserves are currently in need of major repair [6], especially repair related to ventilation problems. This results in chronic exposure to mould and other pollutants which may exacerbate lung disease. Studies of indoor air quality in First Nations homes have shown high values of self-reported [11] and measured [12–14] inhaled air pollutants. Other cultural and environmental conditions exist, such as the fact that many First Nations communities are in areas where there is extensive exposure to environmental pollutants. Northern British Columbia burns more wood per household than anywhere else in the province [14] and has a high prevalence of forest fires [15] both of which contribute to many days per year with high levels of fine particulate matter (PM). Increased exposure to wood smoke and PM is associated with increased respiratory symptoms, use of medications, and health care resources [16]. Additionally, some cultural practices, such as smoking fish and meat, or indoor fires during cultural ceremonies, may increase exposure, albeit for short periods, to inhaled particles.

Despite the presence of multiple individual and community risk factors, there is little information on the prevalence and characteristics of COPD in BC First Nations. The current estimates of COPD prevalence in First Nations communities are based on physician billing records or self-reports of a physician diagnosis. A recent Alberta study found that prevalence estimates of COPD based on billing data were two times higher in First Nations people compared to non-First Nations people [17]. The 2012 First Nations Regional Health Survey stated that ~ 7% of respondents reported they had physician-diagnosed chronic bronchitis [6]. However, the “chronic bronchitis” diagnosis is not a proxy for COPD, as it is a symptom-based diagnosis without measurement of lung function. It is well known that physician billing data or self-reports are not accurate estimates of prevalence -- in the non-Indigenous population, the true prevalence of COPD is approximately three times higher than estimates based on self-report or health administrative databases [18–20]. The Canadian Health Measures Survey found that ~ 70% of individuals with mild to moderate COPD in the overall population have not been diagnosed despite many of those individuals being symptomatic [21].

The higher smoking prevalence in First Nations communities, combined with the cumulative impacts of colonization suggest that the prevalence of COPD in these communities is at least as high as that seen in non-Indigenous communities (which is estimated at 12% of adults 30+ years old) [19]. Without an estimate of the prevalence of COPD in the population, First Nations health services are currently limited in their ability to provide appropriate COPD primary care and chronic disease management services to their members. It would also be useful to understand the current exposure to respiratory risk factors in order to develop strategies to reduce the risks of exposure. Therefore, the purpose of this project is to estimate the prevalence of COPD and characterize current risk factors in several First Nations communities in the province of British Columbia, Canada.

## Methods

The research team is a longstanding partnership between researchers at the University of British Columbia (UBC), the participating First Nations, and Carrier Sekani Family Services (CSFS) – the latter being an organization that provides direct health and social services to First Nations communities in North-Central BC. Community involvement was achieved as the study concept and design was reviewed, revised, and approved by the CSFS Community Advisory Board which is made up of a representative member of the public from each participating First Nation. Research projects undertaken with CSFS require this approval from and engagement with the CSFS Community Advisory Board, which ensures study processes are supported by CSFS, data is owned by the community, and all research provides tangible benefits to the First Nations communities. This decolonizing methodology [22] is mandated in Chapter 9 of the *Tri-Council Policy Statement*, titled “Research Involving the First Nations, Inuit and Métis Peoples of Canada” [23], and forms part of our approved ethics review for this study.

This study will recruit adults 30 years and older from 11 First Nations communities in remote and rural locations in northern British Columbia. The study will consist of detailed questionnaires, lung function measurement, air quality sampling, building assessments, and community-engagement activities. Each eligible adult within a randomly-selected household will be invited to participate and provide informed consent. Data collection will occur between September to April in the 2017–2023 study period in order to obtain air quality measures during high occupancy periods and when indoor heating is likely to occur.

### Sample size and household/individual sampling

We used the Statistics Canada 2016 Census [24], the First Nations Profile [25] and the CSFS community registry to determine our estimated target population to be 1600 adults age 30+ years living in the 11 First Nations. Assuming the prevalence is 13%, a sample size of 220 adults from a population of ~ 1600 would result in a 95% confidence interval of prevalence with a half width no more than 0.05 if the intra-cluster correlation is ≤0.25. This estimate takes into account the fact that household residents are likely to be related meaning that each participant is not independent. On average, there are 2–3 adults per First Nations household [6], therefore approximately 88 households will be needed. We have planned for an additional 20% more households to ensure enough participants.

We will recruit a specific number of people from each community, which will be proportional to the adult population contribution of that community to all the CSFS communities. We estimate that we will be able to recruit 1–2 adults per household. Using a random-number generator, each household is then randomly placed in numbered order. Starting at the top of the list, we then approach the adults in that household with an invitation to participate. If that household declines, we move to the next household on the list. Based on previous Canadian COPD prevalence studies using random population sampling and direct measures of lung function [3, 18, 19], the prevalence of COPD in Canada is 8.1% among all adults, and 15% among ever-smokers. Due to the high prevalence of smoking in First Nations communities, the true prevalence of COPD is likely greater than 8%, so we have used 13% as our estimate for sample size calculations.

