### Data analysis

Using pooled data, descriptive statistics will be used to characterize participants and their communities, including lung function, symptoms, HCU and risk factors. The prevalence of COPD will be calculated as the ratio of COPD cases, based on lung function, to the sampled population. To get a representative estimate of the population prevalence of COPD in remote and rural First Nations communities in BC, we will consider the cluster design and sampling weight, which is the inverse of the likelihood of being sampled. The sampling weights in this study will be computed as the ratio of household size to total population in each community. These weights will be included in the calculation of prevalence with 95% confidence interval estimation. Under-diagnosis of COPD will be estimated by confirming the prevalence of COPD based on spirometry with the medical diagnosis in the EHR.

Secondary analyses will estimate the levels of indoor air pollutants and compare them to consensus guidelines established by the American Society of Heating, Refrigeration and Air-Conditioning Engineers [33, 34] and Health Canada [35]. We will characterize the levels of inhaled pollutants from individual, residential, occupational, cultural/community sources as well as respiratory symptoms, airflow obstruction, and respiratory-related HCU.

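### The stated half-width of at most 0.05 holds on the plan's basis of 2.5 adults per household, but with little margin for the planned weights, and the household count contradicts the expected 1–2 recruits per household

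*Protocol article*

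**What the plan says.** All the planning figures are in the protocol article, section Sample size and household/individual sampling. The precision statement reads "Assuming the prevalence is 13%, a sample size of 220 adults from a population of ~ 1600" and promises a "half width no more than 0.05 if the intra-cluster correlation is ≤0.25". The section adds that the calculation allows for relatedness among household members; it mentions neither weights nor variation in household size.

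The household count follows: "On average, there are 2–3 adults per First Nations household [6], therefore approximately 88 households will be needed", with a reserve of 20% more households. The next paragraph gives a different yield: "We estimate that we will be able to recruit 1–2 adults per household".

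The Data analysis section says that the prevalence and its 95% confidence interval will use sampling weights. It describes these in general as inverse selection probabilities and then defines them: "The sampling weights in this study will be computed as the ratio of household size to total population in each community". The opening of Methods says that every eligible adult in a selected household is invited.

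**The concern.** The half-width is the article's only precision statement and the only justification it gives for 220 adults. It is worded as a bound, so it should hold over the plan's own range of inputs and for the analysis the plan describes. Two things put that in doubt.

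- The planned interval is weighted, and the weights as defined grow with household size. Unequal weights widen the interval, and no allowance for this appears beside the bound.
- The household count and the recruitment expectation rest on different numbers of participants per household. Cluster size drives both the design effect and the number of adults that a given number of households supplies, so the two figures cannot both stand.

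At stake are the precision that readers and the partner communities are told to expect, and whether the stated number of households can supply the stated sample.

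**Working it through.** **Inputs from the protocol article.** Prevalence p = 0.13, n = 220, N = 1600, ICC at its ceiling of 0.25, 2–3 adults per household, 88 households plus 20%, 1–2 recruits per household.

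**Formula.** Half-width = 1.96 × √[p(1−p)/n × DEFF × (1−n/N)]. For equal households of m and no weights, DEFF = 1 + (m−1) × 0.25.

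**1. The plan's own figure.** 0.13 × 0.87 / 220 = 0.000514, and 1 − 220/1600 = 0.8625. So the half-width is 1.96 × √(0.000514 × 0.8625) × √DEFF = 0.0413 × √DEFF. The planning mean is 220/88 = 2.5.

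| Adults per household | DEFF | With finite population correction | Without |
|---|---|---|---|
| 1.5 | 1.125 | 0.0438 | 0.0471 |
| 2 | 1.250 | 0.0461 | 0.0497 |
| 2.5 | 1.375 | 0.0484 | 0.0521 |
| 3 | 1.500 | 0.0505 | 0.0544 |

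The bound is met at 2.5 with the correction. It is just missed at 3, and it is missed at 2.5 without the correction.

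**2. Room left for weights.** A half-width of 0.05 allows a total DEFF of 1.468. Clustering at 2.5 already uses 1.375, which leaves 1.468/1.375 = 1.067, or about 7%.

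**3. Weights proportional to household size k, all adults taking part.** DEFF = E[k] × E[k³(1+(k−1)×0.25)] / (E[k²])², with expectations over households.

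- Half the households with 2 adults, half with 3: E[k] = 2.5; E[k³(…)] = ½(8×1.25 + 27×1.5) = 25.25; E[k²] = 6.5. DEFF = 2.5 × 25.25 / 42.25 = 1.494 and the half-width is 0.0504. Unweighted, the same households give 0.0488.
- Assumed sizes 1–4 (15/40/30/15%): DEFF 1.73, half-width 0.054. Unweighted 0.0497.
- Assumed sizes 1–5 (20/40/20/12/8%): DEFF 2.01, half-width 0.058. Unweighted 0.0507.

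The last two distributions are assumptions; the article gives no spread of household size. These figures leave out the community-population part of the weight.

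**4. The same weights with at most 2 recruits per household and n still 220.** The even 2/3 split gives 0.047, the assumed 1–4 sizes 0.049, and the assumed 1–5 sizes 0.050. The bound is then met or just reached.

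**5. What the household count supplies.** 88 × 1.2 = 105.6, so 106 households. No weights, equal clusters, with the finite population correction:

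| Households | Recruits each | Adults | DEFF | Half-width |
|---|---|---|---|---|
| 88 | 1.5 | 132 | 1.125 | 0.058 |
| 106 | 1.5 | 159 | 1.125 | 0.053 |
| 88 | 2 | 176 | 1.250 | 0.052 |
| 106 | 2 | 212 | 1.250 | 0.047 |
| 147 | 1.5 | about 220 | 1.125 | 0.044 |

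At 1–2 recruits per household, neither 88 nor 106 households reaches 220 adults. At 1.5 each, 220/1.5 = about 147 households are needed.

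**The case against.** The strongest defence is that the plan's arithmetic is right. The bound reproduces at the mean implied by 88 households, it is conditional on the ICC, and every excess above takes the ICC at its ceiling. The misses at 3 per household and for the even 2/3 split are about 0.0005 and vanish when rounded to two decimals. The larger values need household-size spreads that the article does not give, together with full participation, which the article itself does not expect. With 1–2 recruits per household and 220 adults, even the weighted half-width stays at about 0.047–0.050. All of this stands. A reader might infer that the weighted household sample cannot deliver 0.05; the documents do not support that.

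It can also be said that recruitment is by target numbers of people, working down a randomly ordered household list, so 132 or 159 adults is not the planned sample. That is fair: the article does not say that recruitment stops at 106 households. But 88 plus 20% is the number it gives as enough, and under its own expected yield it is not. The comfortable small-cluster precision and the 88-household count cannot be used together.

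Finally, if only some adults in a household take part, a weight of household size over number of recruits is a legitimate adjustment for non-participation. That also stands, but it is not the weight the article defines.

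**Conclusion.** The point holds in limited form. The bound of 0.05 is correct at 2.5 adults per household with equal sizes, no weights and the finite population correction (0.0484). It is not robust: only about 7% of design effect remains, and it is narrowly exceeded at 3 adults per household (0.0505) or under the stated household-size weights with an even 2/3 split and full participation (0.0504). Values of about 0.054–0.058 are scenarios that rest on assumed wider spreads and full participation.

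The firmer part needs only the plan's own figures. The section derives its household count from 2.5 participants each and expects 1–2. At 1.5, 106 households give about 159 adults and a half-width of about 0.053; at the maximum of 2 they give 212. Neither is 220. That the original calculation left out weights and size variation is an inference from the reproduction and from the section's silence; the article does not state it.

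**What to change.** In the sample-size section, use one recruits-per-household figure throughout. At 1.5, choose one of two consistent statements:

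- about 147 households for 220 adults, unweighted half-width about 0.044; or
- 106 households, about 159 adults expected, half-width about 0.053.

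State the half-width as conditional on cluster size, the finite population correction and the weights. Include the weighting effect, and label any household-size spread used for it as an assumption. Compute that effect directly for the weights and cluster sizes assumed, as in step 3 of the working: multiplying a clustering factor by a separate weighting factor understates it when weight and cluster size rise together.

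In the Data analysis section, base the weights on the actual inverse inclusion probability. Every eligible adult in a selected household is invited, so the base weight should not rise with household size. A separate adjustment for non-participation within households may be added.

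The cost is a recalculated sentence and a corrected weight definition. No participants beyond the planned 220 are needed. The downside is either a slightly less favourable stated precision or a larger stated household count, with the fieldwork that goes with it.

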There are many strengths to this project. First, to our knowledge this is the first project in Canada to estimate the prevalence of COPD in First Nations communities using a random-sampling approach to recruitment. Although more labour- and time-intensive, it is the optimal method to ensure the most accurate estimates. Second, we ensure quality control for the spirometry measurements by having: 1) pre- and post-bronchodilator measurements to reduce the risk of errors in categorization; 2) a board-certified respirologist interpreting the results; and 3) frequent quality control assessments throughout the study period. Another strength of this project is that although we collect detailed information on smoking history, we also characterize past and current risk factors beyond cigarette smoking, including childhood exposures, occupational factors, household and outdoor exposures, and the impact of discrimination and access to health services. Finally, our study ensures that the benefits to the community are realized during the study period – we offer lung testing to all adults who are interested; the test results become part of the health record; all lung function abnormalities (COPD and otherwise) are followed up by the primary care team; and spirometers and training are provided to each community for their ongoing use.

In conclusion, this study will provide an estimate of the burden of COPD, including prevalence, and under-diagnosis. We will also characterize risk factors, and respiratory morbidity in First Nations communities in Northern British Columbia. The results from this study will increase the awareness of COPD, and will support health service delivery planning and prevention efforts in the communities. Other First Nations communities in Canada may also find the protocol and subsequent results helpful as they develop chronic disease management strategies for COPD in their communities.

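### The stated prevalence weight has no term for who takes part, so selective non-participation could shift the estimate without showing in its confidence interval

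*Protocol article*

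**What the plan says.** All places are in the Protocol article.

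- **Methods, opening section.** Every eligible adult (aged 30 or over) in a randomly selected household is invited. There is no random choice of one adult within the household.
- **Sample size and household/individual sampling.** Each community has a recruitment number proportional to its adult population. Households are put in random order and approached from the top. On refusal, "If that household declines, we move to the next household on the list". The section cites an average of 2–3 adults per household, and uses it to turn 220 adults into about 88 households plus a 20% reserve. It also says "We estimate that we will be able to recruit 1–2 adults per household".
- **Data analysis.** The weight is described as the inverse of the sampling likelihood and is to be computed as household size over community population. "These weights will be included in the calculation of prevalence with 95% confidence interval estimation". The aim is a representative estimate of population prevalence.
- **Discussion.** Of random sampling, the article says "it is the optimal method to ensure the most accurate estimates".

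**The concern.** The weight goes into the primary estimate and its interval, and its formula is given. As written, it does not use how many households were reached to fill a community's quota, how many eligible adults in an enrolled household took part, or how participants compare with the community in age and sex. Because every eligible adult is invited, any eligible adult not measured is a non-participant and was not left out by random subsampling.

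This matters only if participation is related to COPD. That is plausible, and the article describes features that could pull either way. On-site spirometry with results passed to the care team may attract people with symptoms. Long questionnaires, testing before and after bronchodilator and a home inspection may deter others. The article's own figures show that sample composition matters: 8.1% prevalence among all adults in Canada against 15% among ever-smokers.

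At stake is whether the headline prevalence describes adults aged 30 and over in the 11 communities. A confidence interval reflects sampling error only, so a shift from selective participation would not be visible in it.

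**Working it through.** **1. The plan's precision.** The inputs are all from Sample size and household/individual sampling. For N: "our estimated target population to be 1600 adults age 30+ years living in the 11 First Nations". For p: "so we have used 13% as our estimate for sample size calculations". The planned n is 220, the confidence level is 95%, and the half-width is to be "no more than 0.05 if the intra-cluster correlation is ≤0.25". The average cluster is 2.5 adults, the value that gives 220/2.5 = 88 households.

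Half-width = 1.96 × √[ p(1−p)/n × (1 + (m−1)×ICC) × (N−n)/(N−1) ]

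- p(1−p)/n = 0.13 × 0.87 / 220 = 0.000514
- design effect = 1 + 1.5 × 0.25 = 1.375
- finite population correction = 1380/1599 = 0.863
- half-width = 1.96 × √(0.000514 × 1.375 × 0.863) = **0.0484**

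The stated 0.05 is reproduced. It allows for clustering and a finite population, not for non-response.

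**2. Participation implied within enrolled households.**

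| Recruited | Adults in household | Ratio |
|---|---|---|
| 1 | 3 | 0.33 |
| 1.5 | 2.5 | 0.60 |
| 2 | 2 | 1.00 |

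The midpoint is 60% and the range is 1/3 to 2/2. The article does not say whether the 2–3 adults are all aged 30 or over, so part of the gap may be ineligibility. It does use 2.5 to convert 220 adults aged 30 and over into 88 households.

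**3. How far down the list.** At 1.5 recruits per household, 220 adults need 220/1.5 = 147 households. The plan has 88 × 1.2 = 105.6, about 106 households, yielding 106 × 1.5 = 159 adults. Going further down the list is therefore likely, before any whole-household refusals.

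**4. What the weight would need.** With all households in a community equally likely to be reached, an adult's selection probability is households reached over all households. The formula does not contain households reached. Within an enrolled household, each participant should stand for eligible/participating adults. Household size in the numerator gives the right relative weight between households only if exactly one adult per household takes part. Neither factor says anything about which kinds of adults agreed; that needs outside age-sex counts.

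**5. Illustrative size.** The article gives neither an overall participation rate nor a prevalence for non-participants. Both inputs here are assumptions.

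Bias = (1 − participation) × (prevalence in participants − prevalence in non-participants)

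| Participation (assumed) | Difference 3 points | Difference 5 points |
|---|---|---|
| 60% | 0.4 × 3 = 1.2 | 0.4 × 5 = 2.0 |
| 40% | 0.6 × 3 = 1.8 | 0.6 × 5 = 3.0 |

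The bias is 1.2 to 3.0 points in either direction, or 24% to 60% of the 5-point half-width.

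**6. Cost of unequal weights.** Under an assumed Kish factor (variance inflation from unequal weights) of 1.05 to 1.10: 0.0484 × √1.05 = 0.0496 and 0.0484 × √1.10 = 0.0508.

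**The case against.** The strongest reply is one of scope. This is a journal article, and contact logs, participation reporting and non-response adjustment are often left to the full protocol or analysis plan. What is described is a sampling weight, to which response factors and calibration may be added later; nothing rules them out. That stands as a reason not to fault the article for missing detail. It does not fully answer the point, because the article states how the weight is computed, assigns that weight to the primary estimate and interval, and calls the result representative. Followed as written, nothing corrects for who takes part.

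Four stronger readings are tempting, and the documents do not support them.

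- *Replacement undoes the random selection.* It does not. Taking the next household on a randomly ordered list is equivalent to drawing a longer random list with the same refusals. The remark in the Discussion about the optimal method concerns random recruitment and does not claim full response.
- *The plan expects 60% participation.* That is only the midpoint of a wide range, and the household figure may include adults under 30.
- *The estimate is biased, by about its margin of error.* Bias requires a link between participation and COPD, which is not shown, and the illustration stays below the half-width. Harsher assumptions give more: with 30% participation, a true prevalence of 13% and non-participants at half or twice the participants' prevalence, the bias is +7.0 or −5.3 points. The article supplies none of those inputs.
- *The visits are so long that they deter people.* No visit length is stated.

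**Conclusion.** The point holds as a weakness in a stated rule that is cheap to improve. The article neither shows nor excludes a bias. The weight ignores households reached, eligible adults who do not take part, and the age-sex make-up of participants, while the plan's own figures leave room for substantial within-household non-participation. If participation is related to age, sex or respiratory status, the prevalence will be off by an amount whose sign and size cannot be derived from the document. The 1.2–3.0 points rest wholly on the assumed 40–60% participation and 3–5 point difference. The random ordering of households and the planned precision are both sound as stated.

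**What to change.** 1. **Log outcomes.** For every household reached on the list, record enrolled, declined or not contacted; for every eligible adult in it, record participation. This is hard to recover after fieldwork.
2. **Restate the weight.** Base the selection probability on households reached in each community, and multiply by eligible/participating adults within each enrolled household.
3. **Calibrate.** Rake the weights to counts of adults aged 30 and over by community and by broad age-sex group, taken from the census or the CSFS registry already used for the 1600. Use these as separate margins: 220/11 is only 20 participants per community, too few for a full cross-classification.
4. **Report.** Give household and individual participation rates, and show the uncalibrated prevalence beside the calibrated one.

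The cost is a contact log and one analysis step, provided that the sources supply age-sex counts. The variance rises modestly: under the assumed factor of 1.05–1.10 the half-width becomes 0.0496–0.0508, so the stated 0.05 could be slightly exceeded. Calibrating on community, age and sex does not remove selection on smoking or symptoms; the report should state that as a limitation.
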